### Allocation and blinding

Following initial consent covering the UCHE intervention and subsequent baseline assessments, patients will be randomly assigned to either control or experimental groups in a 1:1 allocation ratio (Fig. 1, Table 3). In line with a single Zelen design [23, 24], patients randomised to the experimental group will be informed about the additional spa therapy intervention and invited to sign an additional consent form; furthermore, these patients can refuse spa therapy, but statistical analysis will be performed on an intention-to-treat basis. Patients allocated to the control group have already consented to the UCHE intervention and will proceed without information on spa therapy; this design is necessary to avoid bias associated with “resentful demoralisation” effects [24].

Allocation is performed using a computer-generated randomisation schedule and stratified by the recruiting investigator/spa (the latter are paired, but separate) and by whether or not the patient has a professional activity. Baseline evaluations and the subsequent randomisation are performed by the recruiting investigators through specific modules administered via a password-protected Internet-accessible electronic case report form (eCRF). The randomisation module will become accessible to investigators only after key elements of baseline data have been entered in the eCRF.

To blind the study as much as possible, follow-up assessments are performed during specific follow-up visits (see Table 3) by an “evaluating” physician, who is different from the “recruiting” investigator. Every attempt will be made to keep evaluating investigators blinded. Specifically, study participants will be instructed to not mention study participation or spa therapy to their evaluating physicians (at the end of the final follow-up visit, the study clinical research associate (CRA) will ask the evaluator a guess-the-group question in order to evaluate the success of blinding). As concerns follow-up care, emergency situations requiring specific unblinding procedures are not foreseen in this protocol. Finally, the statisticians will be blinded, i.e. study arms will be referred to as “A” or “B” when the database is presented for analysis. Unveiling of the study arms will occur after completion of planned statistical analyses.

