### Study setting and population

This study will take place in and around well-established spa centres in Europe (see Table 1). Patients living within a 30-km radius of a participating spa centre and meeting eligibility criteria (Table 2) may participate. Recruitment, enrolment and follow-up visits will occur outside of spa centres (and independent thereof) in participating private offices/clinics, public general hospitals and public university hospitals. The single-payer system in France, where most of the participating spa centres are located, offers medical care to all citizens and residents, and the study population should thus represent a wide range of socioeconomic and rural versus urban backgrounds.

**Table 1 Tab1:** Participating spa centres

Name	Nearby city, Country
Aix-les-Bains	Chambéry, France
Amnéville	Metz, France
Balaruc les Bains	Montpellier, France
Dax	Bayonne, France
Evico Terme	Trentino, Italy
Greoux les Bains	Aix en Provence, France
Hervideros de Cofrentes	Valencia, Spain
Jonzac	Bordeaux, France
Royat	Clermont Ferrand, France
Russian Research Center for Medical Rehabilitation and Balneology	Moscow, Russian Federation
Saint Amand les Eaux	Valenciennes, France
Saint Paul lès Dax	Bayonne, France
Saline Cacica	Northeast Romania
Széchenyi Bath	Budapest, Hungary

**Table 2 Tab2:** Inclusion and exclusion criteria for participants

Inclusion criteria	Exclusion criteria
Adult patient presenting with chronic low back pain: usual pain of the lumbar region lasting for more than 3 months. This pain may radiate to the buttocks, iliac crest, and does not go past the knee [7]	Patients with specific low back pain
Patient presenting upon inclusion with a current pain intensity on a visual analogue scale (VAS) > or = 40 mm.	Patients with severe depression, psychosis
The patient has signed the informed consent form	Patients who have already had a spa treatment in the previous 6 months
Subject aged over 18 and under 80 (years)	Patients with a contraindication for spa treatment^a^
The patient is a beneficiary of a social security programme (national health insurance)	Patients with a professional activity related to balneotherapy (to avoid any conflict of interest)
	Patients with cruralgia or sciatic pain beyond the knee
	Other treatments that may interact according to the investigator’s judgement
	Patients who live more than 30 km away from the spa^b^

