^a^ Immune deficiency, progressive heart disease, progressive neoplasia, infection, chronic bronchitis [14] or foreseeable intolerance to thermal care (intolerance to heat, baths, swimming pool, etc.)

^b^ It will not be convenient to make patients travel more than 60 km per day in their vehicle to deliver between 1 h and 1 h 30 min of outpatient care

In general, eligibility criteria (Table 2) are designed to select for patients with chronic low back pain with a certain level of minimum pain while ruling out cases of specific low back pain. In the case of suspicion of the latter, patients will be aetiologically assessed for rule-out.

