### Interventions and study arms

Two interventions are implemented during this trial (Fig. 1): (1) usual care including a home-exercise programme (UCHE) and (2) spa therapy. The UCHE intervention is designed to be a comparator arm that represents standard care, while limiting care heterogeneity. Patients assigned to the control arm of the study will have the UCHE intervention only, and those assigned to the experimental arm will have both the UCHE intervention and the spa therapy intervention.

The UCHE intervention will correspond to current practice (including the continuation of previous treatments, if applicable) as decided by the patient’s general practitioner. They will also be provided with a practical guide on how to manage back pain (the “back book”), including a recommended home exercise programme [15]. The practical guide on back pain and the exercise programme [15] will be presented to the patient by the recruiting investigators during the enrolment visit and prior to randomisation. Use of the “back book” and daily home exercises will be requested of patients and encouraged throughout the study (Table 3); home exercise observance will be queried at each follow-up visit (Table 3) by asking the patient on what days during the previous week he/she performed the required exercise routine. The recruiting investigator will further encourage and insist that all study participants are to keep trial participation a secret from evaluating investigators.

**Table 3 Tab3:** The LOMBATHERM’ protocol schedule for enrolment, interventions, assessments, and visits for participants

Visit/event:	Enrolment visit^a^		Intervention period	Follow-up visits^b^		
	Baseline	Allocation		1	2	3
Target chronology (days, weeks, months)	D0	D0 (after baseline)	D1–D60	M1^c^ (D28–D60)	M6 ± 4 W	M12 ± 4 W

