The composition of the spa therapy intervention is based on previous results in the domain. Massage [16–21], heat therapy [20] and water exercises [22] have all been demonstrated as helpful for low back pain. Water exercises in particular have similar efficacy to regular exercise regimens, and are sometimes better tolerated [22]. For the present study, the spa therapy intervention consists of 18 consecutive days of spa therapy (3 weeks of treatment, excepting Sundays), that must occur within 60 days of randomisation (Table 3). The latter will always combine mineral water with physical and hydrotherapeutic treatments, including massages, heat and water exercises: (1) pool activities will be carried out by qualified and trained physiotherapists. Small patient groups (limited to 8–15 patients at a time) will participate in pool sessions with 10 min of free bathing and 15 min of supervised exercises in water at 35 °C; (2) underwater massages on painful areas will be performed by qualified and trained physiotherapists in 10-min sessions with water jets at a temperature of 38 °C; (3) mud applications at a temperature of 45 °C will be performed in 15-min sessions, and will include all painful areas (even outside the lumbar region if necessary). In addition to the latter three criteria, further treatments may be added by consensus of spa practitioners in each spa centre. Patients randomised to the spa therapy arm will be invited by the recruiting investigator to keep trial participation and spa therapy a secret from evaluating investigators. Their participation in spa therapy (observance) will be recorded by spa centre staff.

If required, treatment-stopping for home-exercises will be decided via collaboration between the patient and his/her evaluating doctor. Treatment-stopping may occur for spa-therapy in case of an adverse event, is decided on a case-by-case basis by the on-site doctors overseeing spa-therapy, and does not result in study exclusion.

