## Discussion

The LOMBATHERM’ protocol aims to document a thorough range of endpoints highly relevant to the targeted population of patients with low back pain, including changes in pain and symptom acceptability, associated disability, fears and beliefs and quality of life. Should the expected positive effects of spa therapy in addition to usual care be confirmed, a safe, novel physical therapy regimen will be added to the treatment arsenal available for these patients who are difficult to treat.

Care was taken to reduce sources of bias in as much as possible by selecting a clinically relevant primary endpoint and implementing a Zelen randomisation procedure (which eliminates “resentful demoralisation” effects [24]). Further advantages of the Zelen design are an improvement in patient blinding for the control arm, making treatment discussion with the patient more straightforward and closer to “routine” clinical practice, potentially increasing recruitment rates and decreasing post-randomisation withdrawal. However, a single-Zelen design also has a certain limitation that must be taken into account, i.e. the possibility of patient crossover between arms. The latter may dilute the treatment effect within an intention-to-treat analysis, thus providing an underestimated or conservative estimate [24].

Further limitations to the study include a lack of an independent data and safety monitoring board, which was deemed unnecessary due to the low-risk status of this trial. One must also consider the single-blind nature of the protocol, which is understandable given the impossibility of implementing full blinding of the patients receiving spa therapy. Furthermore, there is no way to guarantee the blinding of evaluators, which highly depends on patient collaboration. Nevertheless, the partial blinding of patients (control arm via the Zelen randomisation), the assessing physician, therapists and statisticians have all been addressed. The success of evaluator blinding will therefore be assessed by a guess-the-group question at the end of the final follow-up assessment.

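### The blinding section's instruction not to mention spa therapy names no arm; given to a control patient it reveals the treatment that the single-Zelen design conceals

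*Protocol article*

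**What the plan says.** All references are to the protocol article.

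- **Allocation and blinding**, on controls: they "will proceed without information on spa therapy; this design is necessary to avoid bias associated with “resentful demoralisation” effects". Spa therapy is explained only after randomisation, and only to the experimental arm. Table 3 shows the same order.
- **Allocation and blinding**, on keeping evaluators blind: "study participants will be instructed to not mention study participation or spa therapy to their evaluating physicians".
- **Interventions and study arms**, on the usual-care intervention: the recruiting investigator is to "insist that all study participants are to keep trial participation a secret from evaluating investigators". Spa is not mentioned.
- **Interventions and study arms**, on the spa intervention, with the sentence cut just before its last word: "Patients randomised to the spa therapy arm will be invited by the recruiting investigator to keep trial participation and spa therapy a secret from evaluating".
- **Recruitment and visits**: the advertising leaves spa out, and the first consent covers usual care with home exercise only.
- **Table 2** applies to every candidate before allocation. Its exclusions include "Patients who have already had a spa treatment in the previous 6 months", a contraindication to spa treatment (footnote a adds "foreseeable intolerance to thermal care (intolerance to heat, baths, swimming pool, etc".), work connected with balneotherapy, and living more than 30 km from the spa.
- **Discussion**: the Zelen procedure is credited with removing resentful demoralisation and with "an improvement in patient blinding for the control arm". The only blinding check in Table 3 is a guess-the-group question put to evaluators.

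**The concern.** A single-Zelen design protects the control arm only while controls do not know which treatment they were not offered. An instruction to a control not to mention spa therapy gives that away, because a patient who has never heard of spa in the study has no reason to be told to keep quiet about it.

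The primary outcome is an improvement of at least 30% on a pain scale that the patient scores. A control who learns of the spa arm could report less improvement out of disappointment, which would inflate the contrast. The same patient could instead obtain spa treatment privately, which would dilute it. The Discussion covers only the second direction, where it describes crossover as making the estimate conservative.

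Separately, some exclusions checked before allocation could hint at spa if they are raised clumsily. With the blinding check confined to evaluators, the trial would have no data on whether its claim about control-arm blinding held.

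**Working it through.** **1. The four statements side by side**

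| Place | Who is addressed | What is to be kept from evaluators, or from patients | Compatible with uninformed controls? |
|---|---|---|---|
| Allocation and blinding, Zelen paragraph | Controls | Controls receive no information on spa | This is the rule itself |
| Interventions and study arms, usual care | All participants | Trial participation | Yes |
| Interventions and study arms, spa | Spa arm only | Trial participation and spa therapy | Yes |
| Allocation and blinding, evaluator paragraph | Study participants, no arm named | Study participation or spa therapy | Not if given to a control |

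Three of the four fit together as an arm-specific scheme. The fourth merges the two instructions and drops the restriction to the spa arm. It stands in the section that governs blinding, where site staff would look.

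**2. The exclusions**

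Four of the eight exclusions in Table 2 concern spa. Distance can be judged from the address, and callers are already routed to a recruiter by location. Most contraindications in footnote a (immune deficiency, heart disease, neoplasia, infection, chronic bronchitis) are ordinary medical history. That leaves three items likely to need a question to the patient that could hint at spa: recent spa treatment, intolerance to heat or baths, and balneotherapy work. Asking about past spa use does not by itself say that spa is being tested.

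**3. Could leakage matter? A conditional check**

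Inputs from Sample size: 40% versus 25% response, type I error 4%, 322 patients before and 358 after drop-out (161 or 179 per arm). Sidedness is not stated; two-sided is assumed because it reproduces the plan's figure.

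Plan's own figure: with pooled variance the formula gives 163 per arm, 326 in total. With unpooled variance it gives 160 per arm, 320 in total. The plan states 322, and 322/0.90 ≈ 358. The sample size is reproduced and is not in question.

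Power is approximated by Φ[(|d| − z·s0)/s1], plus the small opposite tail, where d is the difference in proportions, z = z(0.98) = 2.054, s0 = √(2p̄(1−p̄)/n) and s1 = √((p1(1−p1)+p2(1−p2))/n). Example: n = 179, 25% versus 20%, so p̄ = 0.225, s0 = 0.04414, s1 = 0.04406. Then (0.05 − 2.054×0.04414)/0.04406 = −0.92, giving 17.8%, or 17.9% with the opposite tail.

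*Assumption A: spa has no true effect, and awareness lowers control response across the whole arm.*

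| Control response | Chance of significance, 179 per arm | 161 per arm |
|---|---|---|
| 25% (no leakage) | 4.0% | 4.0% |
| 22.5% | 7.2% | 6.8% |
| 20% | 17.9% | 16.4% |
| 17.5% | 37.4% | 34.1% |

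*Assumption B: spa works as planned, and some controls obtain it with full benefit.* Control response is 25% + c × 15 points, where c is the share crossing over.

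| c | Control response | Power, 179 per arm | 161 per arm |
|---|---|---|---|
| 0 | 25% | 83.9% | 79.7% |
| 10% | 26.5% | 74.7% | 69.9% |
| 20% | 28% | 63.5% | 58.7% |

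None of the falls in control response or the crossover shares comes from the documents. The tables show only that leakage would matter if it were widespread, and that the two mechanisms pull in opposite directions.

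**The case against.** The strongest reply is that the sentence under Allocation and blinding is a loose one-line summary. It does not say all participants or both arms. The earlier section sets out the arm-specific scheme in full, and the advertising, the first consent and the timing of disclosure are all consistent with it. This stands as a reading of intent. It does not remove the contradiction, since two versions of an instruction to patients remain and only one is safe to give to a control.

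A reader might infer more: that the Zelen concealment is undone, or that half of the exclusion criteria announce the experimental arm to future controls. The documents do not support either. Table 2 is a list of eligibility criteria, not a script read to patients, and all of its spa-related items can be established without naming spa as the study treatment. How recruiters ask may be set out in the full protocol, the case report form or the patient materials, which are not shown, so its absence from a journal article is not a fault.

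It can also be said that no stated rule requires control awareness to be tested, and that the Discussion speaks only of partial blinding of patients. That is fair; the extra question is a cheap improvement, not the repair of an error. Finally, the conditional figures above presuppose arm-wide effects, and the Discussion already names dilution by crossover. That stands too, so they cannot be used as an estimate of bias.

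**Conclusion.** The point holds as a contradiction within one section: controls are to remain uninformed about spa, yet an instruction naming spa is addressed to study participants without regard to arm. Given as written to a control, it would disclose the experimental treatment in a trial with a patient-reported primary outcome. The correct version is already in the article, so this should be reconciled, not redesigned. The eligibility checks add a possible hint, no more.

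No size can be attached to the effect. A reader might take the conditional figures (up to 37.4% false positives, or power down to 58.7%) as the expected damage. They rest on assumed disclosure and crossover effects that act in opposite directions, so no net bias is established. The conclusion rests on the wording alone and does not depend on those figures.

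**What to change.** 1. In Allocation and blinding, limit the spa part of the secrecy instruction to experimental-arm patients after the second consent. Give all patients only the neutral instruction, already in Interventions and study arms, to keep trial participation from the evaluating physician.
2. Check the exclusions that could hint at spa without presenting spa as the study treatment: recent spa use within a mixed list of past treatments, heat or bath intolerance within the general medical history, and balneotherapy work through an open question on occupation. If the site documents already do this, a sentence saying so is enough.
3. As a cheap addition, once all month-12 assessments are complete, have the clinical research associate ask each control patient whether and when they learned that the study involved spa therapy. Report the proportion beside the evaluators' guesses. Asking last means that the question itself cannot affect an outcome.

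Cost: a changed phrase, neutral wording at screening, one extra question, and slightly less sharp ascertainment of prior spa use. Outcomes, analysis and sample size are unchanged. Recruitment was ongoing when the article was published, so the wording change could protect only later participants, while the closing question could also cover those already enrolled who had not completed month 12.

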We propose to fill this methodological/knowledge gap by implementing a trial with the highest level of evidence possible. Our working hypothesis is that spa therapy in addition to usual care including home exercises (UCHE) will result in greater improvements in pain reduction, associated disability and quality of life in patients with chronic low back pain. It follows that health resource consumption and related costs should also be reduced. The primary objective of this study is therefore to compare the therapeutic effect of UCHE alone versus spa therapy in addition to UCHE for chronic low back pain (Fig. 1). Secondarily, we will also (1) evaluate the therapeutic effects specific to each spa centre, (2) specifically describe effects among subjects who are currently engaged in a professional activity, (3) evaluate treatment tolerance and (4) evaluate per-patient health resource use and associated costs.

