**Harms**						
Tolerance: adverse event characterisation and reporting			*Throughout intervention and follow-up periods*			

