**Blinding success**						
Guess-the-group question for evaluators						✓

*D* day, *M* month, *W* week, *FABQ* Fear, Avoidance, Belief Questionnaire, *EQ-5D-5L* Euroqol Group 5 dimension, 5 level questionnaire

^a^Enrolment visits are performed by recruiting investigators, who are not the same as evaluating investigators

^b^Follow-up visits are performed by evaluating investigators, who are not the same as recruiting investigators

^c^Or just after the end of spa therapy, if applicable

^d^The patient will also be provided with a practical guide on how to manage back pain (the “back book”), including a recommended home exercise programme [15]

^e^Age, sex, duration of current episode of low back pain, signs of spread of osteoarthritis, pain spreading, history of lumbar surgery, need for frequent position changes, bad mood and irritability, sleep disorders due to back pain

^f^Semi quantitative scales that reflect (1) the patient’s and, separately, (2) the physician’s overall opinion concerning the patient’s state of health

^g^Resource use including infiltrations, hospitalizations, physical treatments (massages, traction, physical therapy) and medical imaging of the lumber spine will be tracked

^h^Costs will be estimated using resource-use data gathered during visits and the French National Cost Scale. Indemnities related to days of sick leave will be included in cost estimates

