### Recruitment and visits

Recruitment will be assisted by advertising (not mentioning spa therapy) in the local press and by posting information in local pharmacies, physicians’ offices or clinics. In the case of recruitment difficulties, local companies known to have high rates of workers on sick leave for low back pain may be contacted. Following the advertising campaign, telephone contact between responding, potential study participants and a clinical research technician (CRT) will result in referral to a recruiting investigator (depending on location), who is responsible for obtaining consent and for enrolment, baseline evaluations and randomisation. The enrolment visit will start with an initial presentation and provision of informed consent for the UCHE intervention (Table 3). Following presentation of the “back book” and baseline evaluations, participants will be randomised and those allocated to the experimental arm will be invited to sign an additional consent form for spa therapy. As no biological collections or ancillary studies are foreseen in this protocol, further consent procedures beyond the latter are not required. Appointments will be made for spa therapy (in the next 60 days (maximum) for patients consenting to spa therapy in the experimental arm) and for follow-up visits with evaluating physicians for all patients in both arms at months 1, 6 and 12. The specific assessments required at baseline and during follow-up visits are detailed in Table 3 and closely follow the study outcomes plus the following: demographic data and disease history at baseline, home exercise observance and any required harms reporting. No specific post-trial care (beyond routine care) is foreseen.

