### Harms

Few prospective studies have sought to evaluate the adverse effects and complications that may occur during a spa treatment [42–45]. Due to the absence of control groups, imputability is often not established and few studies clearly describe side effects. Among patients undergoing spa therapy, with or without radon, Franke et al. [39] observed: an increase in pain (7/1), hypertension (2/1), fatigue (2/1) or coloration of the skin and nails (2/0). Gáti et al. [46] observed three cases of respiratory tract infection, one case of cardiac arrhythmia, hypertension and cardiac decompensation, one case of cystitis and one case of gastroenteritis in relation to spa therapy. Another study reports a complete absence of adverse effects [37]. In other publications, adverse effects are not discussed. Based on adverse event reports from the largest studies [47, 48], no serious adverse events are expected. Based on the adverse effects observed during spa treatment for knee osteoarthritis, and in epidemiological studies, we expect to observe benign infections of the upper airways, increased pain or potentially leg erysipelas. A rarer but theoretically possible effect is the occurrence of opportunistic pulmonary infections (legionella) - a few cases and case series were described in the 1980s. These infections have become rare following a change in water disinfection methods in the spa centers [49].

Additional events that may be expected because they are associated with physical exercise in general are respiratory disorders and shortness of breath, cardiovascular disorders (chest pain, myocardial infarction, cardiac arrhythmia, tachycardia, vagal discomfort, hypotension or hypertension, fatigue and injuries (cramps, muscle aches, sprains, strains, tears, fractures)).

Harms reporting will be carried out in compliance with the French regulations in force (or their equivalent in other countries as appropriate) throughout the study (see Table 3). There is no anticipated harm or compensation for trial participation.

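### Post-course harms are to be reported at visits run by evaluators from whom patients must hide the spa, which risks selective under-reporting in the spa arm and leaves attribution open

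*Protocol article*

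**What the plan says.** - **Objective.** The Background lists as a secondary aim "3) evaluate treatment tolerance".
- **Period.** Table 3 has a row "Tolerance: adverse event characterisation and reporting", set to run "Throughout intervention and follow-up periods". No individual visit is ticked.
- **Place.** Recruitment and visits names, among the assessments at baseline and follow-up, "home exercise observance and any required harms reporting".
- **Assessor.** Table 3 footnote b: "Follow-up visits are performed by evaluating investigators, who are not the same as recruiting investigators". This covers months 1, 6 and 12.
- **Secrecy.** Allocation and blinding states that "study participants will be instructed to not mention study participation or spa therapy to their evaluating physicians". Interventions and study arms has the recruiting investigator press all participants to conceal trial participation, and asks spa-arm patients to conceal the spa as well. None of these statements makes an exception for adverse events.
- **Expected harms.** The Harms section anticipates upper-airway infection, more pain, possibly leg erysipelas and, rarely, legionella. It faults earlier studies because causal attribution was often not established.

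**The concern.** Each provision is reasonable alone, but together they pull against each other. The physician who runs the visit at which harms are to be reported is the one person from whom the exposure must be kept. A patient who takes the instruction seriously may leave out an event that cannot easily be described without mentioning the spa, such as a skin infection noticed after mud packs or a pain flare that began in the pool.

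Concealing the trial is asked of both arms. Concealing the spa can only affect the arm that had it. Any withholding from that cause is therefore differential, and it makes the spa look better tolerated than it is. The evaluator also cannot judge imputability, which is the weakness the Harms section criticises in earlier work. The Discussion states that there is no independent data and safety monitoring board, so that second check on harms is absent.

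**Working it through.** The plan gives no harms rate or harms calculation to reproduce. The check is a reading of the sections side by side, followed by one illustration on assumed rates.

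**1. Where post-course harms are picked up.** Spa therapy takes 18 treatment days and must occur within 60 days of randomisation. Month 1 is at D28–D60, or just after the course (Table 3 footnote c). The next scheduled visit is month 6 ± 4 weeks. An event that starts after the month 1 visit therefore first meets a scheduled visit at about month 6, with the blinded evaluator.

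**2. Who knows the exposure there.** The patient knows but is told not to mention it; the evaluator does not know. During the course on-site doctors oversee the spa and may stop it for an adverse event (Interventions and study arms). The article gives them no role afterwards.

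**3. Other channels.** Under Promoting participant retention, the technician contacts patients in the week before each follow-up visit to remind or reschedule, and patients are asked to call the technician if they cannot attend or have other problems. This route does not pass through the evaluator, but the article gives it no explicit harms role.

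**4. Direction of the bias.** Let p_S and p_C be the true event proportions and u the share of spa-arm events not mentioned because of concealment. The reported difference is p_S(1 − u) − p_C. For any u > 0 it is smaller than p_S − p_C, so the shift is always in favour of the spa.

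**5. Illustration only.** Assume p_S = 15%, p_C = 5% and two-sided α = 0.05; none of these is given for harms in the article. Take n = 358/2 = 179 per arm from Sample size. With p₁ = p_S(1 − u), p₂ = p_C, d = p₁ − p₂ and p̄ their mean:

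power = Φ{[d√n − 1.96√(2p̄(1 − p̄))] / √(p₁(1 − p₁) + p₂(1 − p₂))}

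For u = 0: (0.10 × 13.38 − 1.96 × 0.424)/0.418 = 1.21, so power is 89%.

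| u | reported spa rate | reported difference | power |
|---|---|---|---|
| 0 | 15% | 10 points | 89% |
| 25% | 15 × 0.75 = 11.25% | 6.25 points | 58% |
| 50% | 15 × 0.50 = 7.5% | 2.5 points | 16% |

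Here u applies to all spa-arm events. Withholding would mainly concern events after the course, so the overall u would be lower than the share withheld after the course. Table 4 lists no between-arm harms test, so power serves only as a gauge of how quickly a real difference could be obscured.

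**The case against.** The best defence is that the instruction covers participation and the spa, not symptoms. A patient can report an infection, its date and its treatment without saying where it began. Allocation is recorded in the eCRF, so events can be tabulated by arm without the evaluator's knowledge, and an assessor unaware of exposure protects against biased ascertainment. Table 3 sets reporting throughout the study, the Harms section refers to national regulations without naming a reporter, and the full protocol may assign collection to someone else.

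Much of this stands. It defeats the inference, which a reader might draw, that the tolerance objective cannot be answered at all. It also defeats a claim that the three visits are the only route for harms. Three further inferences lack support:

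- That events during the course are over-counted in the spa arm. On-site doctors are present, but the article describes no active questioning about events by them.
- That the protocol forbids disclosure in an emergency. It says only that emergencies needing special unblinding procedures are not expected.
- That a particular share of events will be lost. No figure in the article anchors one.

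The defence does not remove the conflict in the stated text. Harms reporting is placed at visits run by the blinded evaluator, and the secrecy instruction has no exception. A fuller document might add a channel, but the instruction as worded would still deter some spa-arm reports, and the article leaves spa attribution after the course unexplained.

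**Conclusion.** The concern holds in a limited form. As written, the secrecy instruction and the placing of harms reporting at evaluator visits create a risk of selective under-reporting in the spa arm after the course, and the evaluator cannot judge imputability. The direction, in favour of the spa, follows from the design: only one arm has a spa to hide. The size cannot be derived from the article and depends on how literally patients take the instruction. The illustration shows sensitivity under assumed rates and is not an estimate.

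Tolerance is a secondary objective and can still be addressed through reported events by randomised arm. The primary endpoint is untouched. This is a correction worth making, not a flaw that threatens the trial.

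**What to change.** 1. Have the research technician ask a short, identical set of adverse-event questions in both arms during the contact already made in the week before each follow-up visit, and record the answers in an eCRF module closed to the evaluator.
2. State that the harms comparison covers all adverse events by randomised arm, regardless of attribution. It then does not depend on any assessor's view of cause.
3. Reconcile the secrecy wording in Interventions and study arms and in Allocation and blinding with the harms provisions in Table 3, Recruitment and visits, and Harms, so that the instruction does not deter patients from reporting adverse events.

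The cost is slightly longer calls, one eCRF access restriction and a sentence in the patient instruction. Moving these questions away from the evaluator also removes one occasion on which the blind could be broken.
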